# Treating posttraumatic stress disorder in substance use disorder patients with co-occurring posttraumatic stress disorder: study protocol for a randomized controlled trial to compare the effectiveness of different types and timings of treatment

**DOI:** 10.1186/s12888-021-03366-0

**Published:** 2021-09-07

**Keywords:** Post-traumatic stress disorder, Substance use disorder, Prolonged exposure, Eye movement desensitization and reprocessing, Imagery rescripting, Treatment timing, Simultaneous, Sequential, Trauma-focused treatment

## Abstract

**Background:**

Posttraumatic stress disorder (PTSD) and substance use disorder (SUD) have high comorbidity. Although prior research indicated that PTSD can effectively be treated with Prolonged Exposure (PE) in these patients, reported effects are small and treatment dropout rates high. Eye Movement Desensitization and Reprocessing (EMDR) and Imagery Rescripting (ImRs) are other promising treatment options for PTSD, that have not yet been examined in this patient group. Furthermore, it is unclear whether PTSD treatment is most effective when offered simultaneous to or after SUD treatment.

**Methods:**

In this article, the Treatment Of PTSD and Addiction (TOPA) study is described: a Dutch randomized controlled trial (RCT) that studies the effectiveness of PTSD treatment as an add-on to regular SUD treatment in patients with SUD and co-occurring PTSD. Effects of PE, EMDR, ImRs, and a 3-month SUD treatment only condition will be compared, as well as simultaneous SUD/PTSD treatment to sequential SUD/PTSD treatment. The primary outcome measure is PTSD symptoms. Secondary outcomes are: treatment completion, psychological distress, substance use, interpersonal problems, emotion dysregulation, and trauma-related emotions guilt, shame, and anger.

**Discussion:**

This study is the first to compare effects of PE, EMDR, and ImRs in one study and to compare simultaneous SUD/PTSD treatment to sequential SUD/PTSD treatment as well. This RCT will provide more knowledge about the effectiveness of different treatment strategies for PTSD in patients with co-occurring SUD and will ultimately improve treatment outcomes for patients with this common co-morbidity worldwide.

**Trial registration:**

Netherlands Trial Register (NTR), Identifier: NL7885. Registered 22 July 2019.

## Background

### PTSD and SUD comorbidity

Posttraumatic stress disorder (PTSD) and substance use disorder (SUD) often co-occur, with an estimated prevalence of SUD amongst individuals with PTSD of 46% in an epidemiologic study in the United States [1]. Studies in patients with SUD have reported rates of current PTSD amongst individuals with SUD of 25 to 34% [2, 3], with the highest rates reported in SUD patients with both alcohol and drug use disorders [3]. There are different causal pathways that may explain this high co-occurrence, that are not mutually exclusive. Firstly, SUD could lead to an increased risk of developing PTSD by leading a more risky lifestyle, which increases chances to experience traumatic events (e.g. being assaulted violently or sexually when being under influence of substances) [4]. Secondly, several studies indicated that PTSD can lead to the development of SUD as people attempt to self-medicate PTSD symptoms by using substances (e.g. [4, 5]. Thirdly, the onset or maintenance of both SUD and PTSD could be related to a shared underlying factor such as genetic vulnerability [6, 7].

### PTSD treatment

Prolonged Exposure (PE) and Eye Movement Desensitization and Reprocessing (EMDR) are both first line treatments for PTSD that have been studied extensively and shown to be effective treatments for reducing PTSD symptoms [8], also in patients with severe co-occurring disorders such as psychotic disorders [9]. Unfortunately, despite the high prevalence, patients in treatment for SUD are often excluded from randomized controlled trials (RCTs) evaluating PTSD treatments [10]. However, several studies have been conducted to examine the effectiveness of PE specifically in patients with co-occurring PTSD and SUD. A Cochrane review indicated that trauma-focused exposure-based interventions, such as PE, have consistently been found to be effective in reducing PTSD symptoms in patients with SUDs, when added to regular addiction treatment [11]. However, trauma-focused exposure-based interventions are found to be less effective in individuals with PTSD and SUD compared to individuals with PTSD alone. This may be related to the finding that, when trauma-focused interventions are added to regular addiction treatment, treatment drop-out rates are higher than in regular addiction treatment [12]. Furthermore, clinicians perceive individuals with both disorders as more difficult to treat than individuals with either PTSD or SUD alone [13].

Hitherto it is unknown how treatment completion can be increased in this difficult to treat group of patients. In a recent RCT a 90-min trauma-focused motivational enhancement session was added prior to PE therapy in order to increase treatment completion and effectiveness of PE in patients with PTSD/SUD. Unfortunately, adding this session did not lead to better PE retention than PE alone [14].

In patients with co-occurring PTSD/SUD, the effectiveness of EMDR has been studied in only one randomized pilot study [15]. Although this study had a sample size of only 12 patients, it indicated that adding EMDR to regular addiction treatment leads to a significant reduction of PTSD symptoms [15]. However, further research with a larger sample size is essential to draw further conclusions on the effectiveness of EMDR in this patient group. Possibly, treatment drop-out rates may be lower in EMDR compared to PE, since EMDR requires only brief activation of exposure to the traumatic experiences instead of prolonged reliving of traumatic experiences. The same accounts for yet another promising treatment option, namely Imagery Rescripting (ImRs), although this treatment has never been studied in patients with both PTSD and SUD.

ImRs is a therapy that is becoming increasingly popular for treating PTSD and other disorders. A meta-analysis of 19 studies showed that ImRs is effective in reducing aversive imagery and related psychological complaints, with large effects obtained in a small number of sessions [16]. In chronic PTSD patients, the addition of ImRs to PE led to a significant reduction of treatment drop-outs and better effects on anger control, externalization of anger, hostility and guilt compared to PE alone [17]. Furthermore, ImRs was found to be effective in patients who did not respond well to PE and predominantly experienced non-fear emotions like shame, guilt and anger [18]. Two subsequent studies found that ImRs is effective as a stand-alone treatment for PTSD after childhood abuse [19, 20]. Furthermore, two meta analyses both indicated that ImRs has positive effects in the treatment of nightmare frequency, sleep quality and PTSD symptoms [21, 22]. A recent RCT directly compared ImRs to EMDR in patients with PTSD from childhood experiences and found that both treatments are equally effective [23].The release of the *Diagnostic and Statistical Manual of Mental Disorders 5* (DSM-5) [24] has expanded the scope of criteria of PTSD beyond a fear-based concept, considering that a traumatic event can also be followed by shame, guilt and/or anger. Trauma-related shame and guilt seem to play a central role in the maintenance of PTSD symptoms, by contributing to emotional aversiveness of the trauma memory. Higher degrees of shame and guilt in PTSD are associated with depression and anxiety symptoms [25], and with higher levels of PTSD symptoms through treatment [26]. A review illustrated that especially shame is a notable component of PTSD and that reducing shame may increase the effectiveness of the treatment of PTSD symptoms [27]. Individuals with a history of childhood trauma and neglect experience more intense feelings of shame and sadness than healthy controls without childhood abuse and neglect, whereas higher levels of shame and sadness are related to substance use [28]. This substance use is generally hypothesized to be an emotion regulation strategy, therefore childhood trauma may increase the risk for developing SUD at least partially through increased levels of shame and sadness [28]. Given the above described effectiveness in reducing drop-out and feelings of anger, shame and guilt in patients with PTSD, ImRs is a promising approach for treating PTSD in patients with SUDs.

In summary, although prior studies indicated PE is an effective PTSD treatment for patients with co-occurring PTSD and SUD, effects were small and treatment drop-out rates were high. EMDR and ImRs are other promising treatment options for PTSD, that have not yet been examined in this difficult to treat patient group. Furthermore, head-to-head comparisons of these active PTSD treatments are scarce, and completely lacking in SUD/PTSD patients.

### Treatment order

In most published studies in which a trauma-focused treatment was added to SUD treatment, it is unclear whether treatments for PTSD and SUD were delivered simultaneously (starting at the same time) or sequentially (starting PTSD treatment after finishing SUD treatment) [7, 29] A Dutch study showed that simultaneous PTSD/SUD treatment can be safely implemented in inpatient as well as outpatient addiction care without negative effects on SUD treatment [30]. Yet another study showed that delivering PE and SUD simultaneously did not lead to deterioration of PTSD or SUD symptoms. When looking at individual changes during therapy with change analyses instead of reliance on means, patients who did experience an increase of PTSD or SUD symptoms somewhere during treatment, still improved on these symptoms at the end of treatment [31]. Dutch guidelines recommend simultaneous treatment of PTSD and SUD [29], whereas international guidelines (e.g. APA; ISTSS; NICE) do not address the issue of treatment order. However, treatment facilities often promote sequential treatment in which PTSD is treated after SUD treatment is finished. A previous study indicated that some clinicians working in addiction facilities strongly argue against simultaneous treatment [32]. These clinicians report to have too limited time and resources to adequately treat PTSD and report to believe simultaneous treatment to be counterproductive and harmful by eliciting craving and relapse. In contrast, in a more recent vignette study among clinicians, most clinicians preferred simultaneous SUD and PTSD treatment, because they believe that PTSD complaints maintain the SUD. However, most clinicians indicated that at their own workplace they found it difficult to implement simultaneous treatment due to a limited amount of inpatient facilities as well as lack of expertise [33]. Recently, simultaneous treatment has been directly compared to phased treatment in an RCT [34]. In this study, the PTSD treatment consisted of PE whereas the SUD treatment consisted of Motivational Enhancement Therapy. In the phased treatment condition, the PTSD treatment started after 4 (out of 12) weekly sessions of SUD treatment. In contrast to the hypothesis, no differences in PTSD symptoms, SUD symptoms and treatment drop-out rates were found between the two groups [34].

Besides studies that have examined PTSD treatments that were added to SUD treatments, there are several studies that have examined the effectiveness of integrated treatments that integrate SUD and PTSD components within one treatment. Most consistent evidence is found for COPE (concurrent treatment of substance use disorders and PTSD using prolonged exposure), that includes motivational enhancement and CBT for SUD, psychoeducation relating to both disorders, and PE for PTSD [11, 35]. Another integrated treatment is Seeking Safety, a non-trauma-focused intervention that aims to reduce both PTSD and SUD by focusing on safe coping skills [36]. The previously mentioned Cochrane review found no improvement for PTSD severity when non-trauma-focused interventions were compared to usual care or to another active psychological therapy [11]. In summary, although guidelines recommend simultaneous treatment for PTSD and SUD, many therapists argue against this approach. Furthermore, studies directly comparing simultaneous with sequential treatment are lacking. More knowledge about this subject is necessary to improve treatment guidelines for co-occurring PTSD and SUD and enhance treatment outcomes of patients with this common comorbidity.

### Current study

This paper describes the study design of the Treatment Of PTSD and Addiction (TOPA) study, a Dutch RCT in patients with co-occurring PTSD and SUD who will receive PTSD treatment as an add-on to regular SUD treatment.

The primary objectives of this study are:
To compare effectiveness of PE, EMDR, and ImRs as add-on to regular SUD treatment with SUD treatment only in patients with co-occurring PTSD/SUD.To compare effectiveness of simultaneous SUD/PTSD treatment with sequential SUD/PTSD treatment in patients with co-occurring PTSD/SUD.To explore differential effectiveness between active PTSD treatments (PE vs. EMDR; PE vs. ImRs, EMDR vs. ImRs) in patients with co-occurring PTSD/SUD.

We expect that at 3-month follow-up, all trauma focused therapies will have led to a stronger reduction of the primary outcome PTSD symptoms than the SUD treatment only condition (objective 1). In addition, we expect that, compared to the SUD treatment only condition, all trauma focused therapies will have led to a stronger reduction of the following secondary outcomes: psychological distress, substance use, interpersonal problems, emotion dysregulation, guilt, shame and anger. We expect a greater reduction of PTSD symptoms in the simultaneous treatment condition compared to the sequential treatment condition at 6 and 9-month follow-up (objective 2). We have no specific hypothesis about the direction of the differences in effectiveness between the three active PTSD treatments (objective 3).

Due to the COVID-19 outbreak in March 2020, temporary changes in both treatment as well as assessments had to be made, as the regular face-to-face contacts were temporarily not allowed at the treatment facility center where this study is conducted. In this article the original design of the study is described in the method section. At the end of the method section, all adjustments that were made due to COVID-19 outbreak are described.

## Methods

### Design

This study is a single blind 6-arm randomized controlled trial, consisting of 3 arms for simultaneous SUD/PTSD treatment with the PTSD treatments consisting of PE, EMDR, and ImRs, and 3 arms for sequential SUD/PTSD treatment with the PTSD treatments also consisting of PE, EMDR, and ImRs. Within the first 3 months after baseline, the three sequential treatment arms together form the SUD treatment only condition, as is depicted in the trial flow (Fig. 1). First, patients are randomly allocated to simultaneous PE, EMDR, or ImRs, or the SUD treatment only group. Subsequently, patients in this last group are randomly allocated to sequential PE, EMDR, or ImRs. The study is conducted at two departments of Jellinek. Jellinek is a Dutch addiction treatment facility center, offering both intramural and extramural addiction treatment. The duration of the study is planned to be 3.5 years, from inclusion of the first participant until the last follow-up measure of the final participant. The research protocol has been approved by the Medical Ethical Committee of the Amsterdam Academic Medical Centre (AMC) and the trial has been pre-registered at the Netherlands Trial Register (NTR L7885). The study is currently running.

**Fig. 1 Fig1:**
[figure not shown]
Flow chart of the study design. Abbreviations: SUD: Substance Use Disorder; PE: Prolonged Exposure; EMDR: Eye Movement Desensitization and Reprocessing; ImRs: Imagery Rescripting. Note T0–3 are subsequently the baseline assessment, and assessments at 3 month, 6 month and 9 month follow up

### Participants

Participants are recruited at the Jellinek Center in Amsterdam and Utrecht. Study participants are patients who apply for SUD treatment at the addiction treatment center, for whom treatment of co-occurring PTSD is also indicated. All patients treated in the two participating locations are adults (18 years of age or older), and both males and females can participate in the study. The criteria for inclusion in the study are a) age 18 years or older; b) SUD(s) according to the DSM-5 (American Psychiatric Association, 2013), with a primary diagnosis involving one of the following substances: alcohol, cannabis, cocaine (snorting), amphetamine, benzodiazepine, opioid; c) PTSD according to the DSM-5 criteria; d) sufficient understanding of the Dutch language to be able to fill out Dutch questionnaires and follow therapy in Dutch. The exclusion criteria are: a) acute psychotic disorder; b) mental retardation or cognitive impairment (estimated IQ < 70); c) current physical or sexual abuse or death threats; d) current acute suicidal behavior (high suicide risk and suicide attempt in the last 3 months); e) life threatening self-injury; f) homelessness; g) involvement in a compensation case or legal procedures concerning admission or stay in the Netherlands, h) involvement in legal procedures regarding the index trauma, i) engagement in any other current PTSD treatment.

### Sample size

First, we calculated the required sample size for the comparison between the three types of active PTSD treatments. Second, we calculated whether that sample size will provide sufficient power to compare the two timings of PTSD treatment. Three pairwise comparisons will be conducted between the active treatment arms (ImRs vs. PE, ImRs vs. EMDR; PE vs. EMDR). To detect a small-to-medium effect size (f = 0.15) in a pairwise comparison of pre-post change between two active treatment arms, with Bonferroni-corrected alpha = 0.0167, power = 0.85 and within-person correlation coefficient = 0.60, 54 participants are needed per arm. To make three pairwise comparisons 3 * 54 = 162 participants are needed. The allocation ratio between sequential and simultaneous PTSD treatment is 1:3. With *n* = 41 in sequential treatment and *n* = 121 in simultaneous treatment, power is 99% to detect a small-to-medium effect size (f = 0.15) in a comparison of pre-post change between simultaneous and sequential treatment, with alpha = 0.05, and within-person correlation coefficient = 0.60. To detect a small effect (f = 0.10) power is 81%. We expect 20% of the participants to drop out of the study, therefore in total 204 participants will be included in the study.

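### The timing power of 99% and 81% at 41 versus 121 takes no account of the 1:3 split; for the effect f denotes in the equal-arm calculation of the same paragraph, power is about 96% and 69%

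*Protocol article*

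**What the plan says.** The Sample size section first sizes the trial for the pairwise comparisons between PTSD treatments. At f = 0.15 it states: "with Bonferroni-corrected alpha = 0.0167, power = 0.85 and within-person correlation coefficient = 0.60, 54 participants are needed per arm". Three arms of 54 make 162 patients.

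It then checks whether 162 is enough for the timing comparison. "The allocation ratio between sequential and simultaneous PTSD treatment is 1:3", and "With *n* = 41 in sequential treatment and *n* = 121 in simultaneous treatment, power is 99% to detect a small-to-medium effect size (f = 0.15"). The test is described as being "in a comparison of pre-post change between simultaneous and sequential treatment", "with alpha = 0.05, and within-person correlation coefficient = 0.60". The section adds: "To detect a small effect (f = 0.10) power is 81" per cent.

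It names no software, formula or sidedness, and does not say whether f is weighted by group size. The 162 is the number after dropout: "We expect 20% of the participants to drop out of the study, therefore in total 204 participants will be included in the study".

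Timing is Objective 2, listed among the primary objectives under Current study, with a directional expectation in favour of simultaneous treatment. Under Methodological considerations, low power for small differences is acknowledged for types of PTSD treatment only.

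**The concern.** A two-group comparison loses precision when the groups are unequal. At 41 versus 121 the information is about three quarters of that from 81 versus 81. A power figure printed next to those group sizes should reflect the loss, yet 99% and 81% are the values that an equal split of 162 would give.

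The figure that matters is the one at f = 0.10. It is the only support in the article for adequate power at a small timing effect, and it lies just above the usual 80%. Because the stated limitation on small differences leaves timing out, a reader of a null timing result could believe that a difference of 0.40 SD had an 81% chance of being detected. On the basis used for planning, that chance is about 69%.

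**Working it through.** **Inputs, all from the Sample size section:** groups of 41 and 121 (N = 162); alpha 0.05, taken as two-sided; within-person correlation rho = 0.60; two measurements (pre and post); f = 0.15 and 0.10.

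**1. Identify the formula.** For the group-by-time interaction with two groups and two measurements, the noncentrality is lambda = f² × N × 2 / (1 − rho), with 1 and N − 2 degrees of freedom. For the pairwise comparison at alpha 0.0167, this gives 85.2% power with 54 per arm and 84.4% with 53. It therefore reproduces the article's 54 per arm at 85% power. The formula contains total N but no allocation term.

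**2. Reproduce the stated timing power.** With N = 162 and alpha 0.05:
- f = 0.15: lambda = 0.0225 × 162 × 2 / 0.4 = 18.225, power 98.9% (stated 99%).
- f = 0.10: lambda = 0.01 × 162 × 2 / 0.4 = 8.10, power 80.8% (stated 81%).

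**3. Translate f into a difference.** In equal groups, f places each of the four group-by-time cells f SD from no interaction. The groups then differ in change by 4f: 0.60 SD at f = 0.15 and 0.40 SD at f = 0.10. The SD of change is √(2 × (1 − 0.60)) = 0.894.

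**4. Apply the actual split to the same differences.** Lambda is multiplied by 4 × 41 × 121 / 162² = 0.756, which corresponds to a balanced trial of about 162 × 0.756 = 122 patients.

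| Difference in change | Lambda at 41/121 | Power at 41/121 | Stated |
|---|---|---|---|
| 0.60 SD | 18.225 × 0.756 = 13.78 | 95.8% | 99% |
| 0.40 SD | 8.10 × 0.756 = 6.12 | 69.1% | 81% |

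A two-sample t-test on change scores gives identical values. A simulation of 20,000 trials gives 95.6% and 68.8%. At 0.40 SD the chance of missing the effect is 31%, not 19%.

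**5. What the stated figures would mean at 41/121.** If f is defined with group-size weights, lambda keeps its value from step 2 and 99%/81% are correct. The difference behind each f must then grow by 1/√0.756 = 1.15: from 0.60 to 0.69 SD at f = 0.15, and from 0.40 to 0.46 SD at f = 0.10.

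**6. One-sided test.** At 41/121 a one-sided 0.05 test gives about 98.1% and 79.7% (normal approximation), which do not round to 99% and 81%. No one-sided test is stated.

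**7. Baseline-adjusted analysis.** At 41/121 and 0.40 SD, with 1/41 + 1/121 = 0.03265 and the normal approximation:
- One follow-up: residual variance 1 − 0.60² = 0.64; 0.40 / √(0.64 × 0.03265) = 2.77; power about 79%.
- Mean of two follow-ups, correlated 0.80 with each other (assumed): residual variance 0.90 − 0.36 = 0.54; ratio 3.01; power about 85%.
- The same with follow-ups correlated 0.60 (assumed): residual variance 0.80 − 0.36 = 0.44; ratio 3.34; power about 91–92%.

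**The case against.** **The effect is given as f, not as a mean difference.** With a group-size-weighted f the printed figures are right at 41/121, so it cannot be shown that the authors assumed equal groups. This stands. A reader might infer from step 2 that the power was calculated for an 81/81 split, but the article names no formula or software, and the match is equally compatible with a weighted f. The weighted reading does not rescue the paragraph as written, however. The same f = 0.15, under the same verbal label, would mean 0.60 SD in the pairwise comparison and 0.69 SD in the timing comparison, and nothing tells the reader so.

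**The planned analysis is not a change-score test.** Objective 2 uses a mixed model with baseline CAPS-5 as covariate, an overall effect, and contrasts at 6 and 9 months. Step 7 shows that this could reach 85% or more for the overall effect at 0.40 SD, if the effect is constant over the two follow-ups and the assumed correlations hold. This also stands, and it rules out a stronger reading that is tempting: that the trial lacks adequate power for a small timing effect. It does not make the printed 81% correct, because that figure is expressly tied to pre-post change. A single time point still gives only about 79%.

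**The consequence is small.** The sample size was set by the pairwise comparisons, and the timing power is a check on it. At the effect size common to both calculations, 96% is still ample. This stands and limits the weight of the point.

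**Conclusion.** The timing power is misleading as written. For the difference in change that f denotes in the equal-arm calculation of the same paragraph, 41 versus 121 gives about 96% instead of 99%, and 69% instead of 81%. The 3-point shortfall at f = 0.15 has no practical effect. The 12-point shortfall at f = 0.10 takes the figure below 80%. Read the other way, with f weighted by group size, the percentages hold but the detectable difference is 15% larger than the label suggests, and this is not disclosed.

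The conclusion assumes two-sided alpha 0.05, rho 0.60, two measurements and 162 patients with data. It concerns the power statement. It does not show that the planned mixed model is underpowered, and it does not affect the 54 per arm, the 162 or the 204. The severity is moderate.

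**What to change.** Replace the two power figures with a statement that gives the difference as well as f, for example:

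> With n = 41 and n = 121, two-sided alpha 0.05 and rho 0.60, power for a difference in pre-post change of 0.60 SD (f = 0.15 in equal groups) is 96%, and for 0.40 SD (f = 0.10 in equal groups) it is 69%; 81% power corresponds to 0.46 SD.

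If a weighted f was intended, say so and give the 0.69 and 0.46 SD that it implies. The power of the baseline-adjusted model could be added: about 79% at 0.40 SD for a single follow-up, and higher for the average of two, with the correlation assumptions stated. Under Methodological considerations, extend the limitation on small differences to the timing comparison.

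The cost is a few sentences. No patient is added, and neither the allocation nor the analysis changes. The stated power becomes less favourable.
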